#### 4.2.6 Sleep diary

Following the initial screening, potential participants will be asked to complete an electronic (web-based) sleep diary for four (two + two) weeks.

Five variables will be measured on a daily basis:

- Latency to sleep onset
- Number of night awakenings
- Total sleep time
- Quality of sleep
- Energy level the following day

These variables have been used and cited in the literature as being important measures of sleep. The response options that are used are modified from those used by Coxeter and colleagues in the following ways: We have used seven categories for all five questions for consistency and to facilitate interpretation relative to what has been found to be a clinically important mean difference on 7-point scales. We have added an additional category at the upper end of sleep latency and we have used half hour intervals for total sleep time under five hours to pick up what are likely to be meaningful differences for these two outcomes, based on clinical experience. Finally, a question on the level of perceived refreshment post-slumber is not included because feelings of grogginess are common after awakening and this question has not been found to be helpful in clinical practice.

In addition the diary will include questions about

- Adverse events
- Concomitant medication
- Number of tablets taken

An automated email message will remind participants who have not completed their sleep diary by 1 p.m. each day to do so.

#### 4.2.7 Global assessment score

At Visit 4 each participant will be asked to indicate for each of the five listed variables and globally whether they perceived a change for the two weeks during which they took tablets compared to the two weeks before.

#### 4.2.8 Adverse events

See section 6.3, below.

### 4.3 Scheduling of procedures

**4.3.1 Visit 1 (Day 0; Screening)**

- written informed consent
- control of inclusion and exclusion criteria
- concomitant medication
- PSQI

**4.3.2 Visit 2 (Day 10; Randomisation)**

- confirmation of inclusion and exclusion criteria
- assessment of sleep diary compliance
- randomisation
- shipment of study medication
- adverse events (daily registrations, sleep diary)
- concomitant medication (daily registrations, sleep diary)

**4.3.3 Visit 3 (Day 15; Start of treatment)**

- first day of study medication
- adverse events (daily registrations, sleep diary)
- concomitant medication (daily registrations, sleep diary)

**4.3.4 Visit 4 (Day 28; End of treatment)**

- global assessment score
- return of remaining tablets and/or study medication box
- adverse events (daily registrations, sleep diary)
- concomitant medication (daily registrations, sleep diary)

## **5 STUDY TREATMENT**

### **5.1 Study treatment and comparator**

The following treatment supplies will be used in the study:

*Study treatment:*

Coated Valerina Forte tablets (200 mg extract per tablet, 3 tablets corresponding to 3600 mg *Valeriana officinalis*).

*Comparator:*

Placebo: Coated tablets matching Valerina Forte in terms of appearance, smell and taste.

### **5.2 Supply, packaging, labelling, handling and storage**

Participants who qualify for randomisation at Visit 2 will receive study medication for 2 weeks (3x20 tablets in blister package). To allow time for shipment, first treatment dose is not to be taken until Visit 3.

The study treatment will be labelled with information according to GMP annex 13 and local regulation.

The study treatment will be stored in a pharmacy at room temperature in a secure area protected from unintended use, and shipped to the participant upon confirmation from the investigator that the participant fulfils the randomisation criteria. The study treatment will be sent as a registered letter, requiring the participant to confirm receipt by signature. The participant must enter the randomisation code on the study treatment box to verify that s/he has received the correct package.

The pharmacy will maintain detailed drug dispensing lists.

### 5.3 Dosage and administration

The participants are to swallow 3 tablets every night.

The optimum dose of valerian is unknown. The European Medicines Agency (EMA) final proposal for a Core Data for *Valerianae radix* (<http://www.emea.eu.int/pdfs/human/hmpc/001499en.pdf>) recommends a single dose of 2 to 3 grams half an hour to one hour before bedtime with an earlier dose during the evening if necessary. Three tablets of Valerina Forte, a 200 mg extract (1:6) per tablet, correspond to 3600 mg *Valeriana officinalis*. This is slightly more than the dosage recommended by EMA, but less than the maximum dose recommended by the manufacturer (4 tablets) and far below the maximum recommended daily dose of nine grams.

In previous randomised trials using repeated doses, the amount of extract taken per day has ranged from 450 to 1215 mg. Single dose studies have used quantities ranging from 60 to 900 mg. In two trials doses of 450 and 900 mg were compared with placebo. They each found both doses of valerian to be superior to placebo but not different to each other, suggesting that 450 mg may be a sufficient dose for an acute effect. The extraction ratio of these extracts was, however, not reported, so it is unclear how much *Valeriana officinalis* was administered, and it was found in N-of-1 trials that 450 mg (equivalent to 2 grams of dry root and rhizome) was not effective, perhaps due to that being a relatively small dose. We are therefore testing a larger dose to ensure the best possibility of observing an effect, if valerian is effective, and because there seems to be no evidence of an increased risk of side effects with the higher dose. Up to now reports of adverse events in randomised trials of valerian have been scarce and those that have been reported have been mild and similar to those experienced with placebo.

### 5.4 Duration of treatment

Participants will be treated for a maximum of two weeks.

### 5.5 Concomitant medication

Any medications (prescription only as well as OTC drugs) necessary for the participant's welfare that are not listed among the exclusion criteria (i.e. hypnotics), and which do not interfere with the effectiveness evaluations, are permitted given that they are carefully documented in the applicable diary page.

Investigational new drugs (i.e. drugs that are not marketed in the local market) will not be co-administered with the study medications during the entire period of the study.

### 5.6 Study medication accountability

The participants will each day record in their diaries the number of tablets taken. Upon completion of the study, the participants will be asked to return remaining tablets and the box to the pharmacy. 18 tablets should be remaining in case of 100 % compliance. A pre-paid, return-addressed envelope will be enclosed with the study medication.

Accountability forms will be completed by the pharmacy and compared with the information given by the participants in the diaries.

## 6 RESPONSE VARIABLES AND ENDPOINTS

### 6.1 Assessment of effectiveness

#### 6.1.1 Primary effectiveness variable

- Proportion of participants in each group with an improvement in self-assessed quality of sleep of  $\geq 0.5$  units between the average score for the 2 weeks before and 2 weeks during treatment

#### 6.1.2 Secondary effectiveness variables

- Proportion of participants in each group with an improvement of  $\geq 0.5$  units between the average score for the 2 weeks before and 2 weeks during treatment for each of the four variables:
  - sleep latency
  - number of awakenings
  - total sleep time
  - energy level during the day
- Mean changes in the five outcomes listed above.
- Global self-assessment

If a difference is seen between the treatment groups for the primary and secondary variables, the following explorative variables will be analysed.

- Proportion of participants in each group with any improvement in mean difference (i.e. all score changes  $> 0$ ) between the average score for the 2 weeks before and 2 weeks during treatment for each of the five variables:
  - quality of sleep
  - sleep latency
  - number of awakenings
  - total sleep time
  - energy level during the day
- Difference in the profile of the five endpoints during the intervention period taking into account the baseline period, including a potential time effect.

### 6.2 Assessment of safety

Safety will be assessed by evaluation of registered adverse events, see section 6.3.

### 6.3 Adverse events and Serious Adverse Events

#### 6.3.1 Definitions of Adverse Events

##### Seriousness

Adverse Events (AE): any undesirable experience occurring to a participant during a clinical study, whether or not considered related to the investigational study medication(s).

All Adverse Events must be recorded in the sleep diaries

**Serious Adverse Events (SAE)** are defined as: an adverse experience that is fatal, life-threatening, disabling or which results in-patient hospitalisation or prolongation of hospitalisation, a congenital anomaly or occurrence of malignancy.

**Unexpected Adverse Event:** an experience not previously reported in the product information sheet or similar documents.

### **Severity**

**Mild:** the adverse event is transient and easily tolerated.

**Moderate:** the adverse event causes the patient discomfort and interrupts the patient's usual activities.

**Severe:** the adverse event causes considerable interference with the patient's usual activities, and may be incapacitating or life-threatening.

### **Relationship to study medication**

#### **Unrelated:**

This category is applicable to those adverse events, which, after careful medical consideration at the time of evaluation, are judged to be clearly and incontrovertibly due to extraneous causes (disease, environment, etc.) and do not meet the criteria for study medication relationship listed under remote, possible or probable.

#### **Unlikely:**

In general, this category is applicable to those adverse events, which, after careful medical consideration at the time they are evaluated, are judged to be remotely related to the test study medication. An adverse event may be considered remote if, or when, for example: (i) it does not follow a reasonable temporal sequence from administration; (ii) it could readily have been produced by the patient's clinical state, environmental or toxic factors, or other modes of therapy administered to the patient; (iii) it does not follow a known response pattern to the suspected study medication; (iv) it does not reappear or worsen when the study medication is re-administered.

#### **Possible (must have first two criteria):**

This category is applicable to those adverse events, which, after careful medical consideration at the time they are evaluated, the connection with the test study medication administration appears unlikely but cannot be ruled out with certainty. An adverse event may be considered possible if, or when: (i) it follows a reasonable temporal sequence from administration; (ii) it could readily have been produced by the patient's clinical state, environmental or toxic factors, or other modes of therapy administered to the patient; (iii) it follows a known response pattern to the suspected study medication; (iv) it does not reappear or worsen when the study medication is re-administered.

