#### **Probable (must have first three criteria):**

This category is applicable to those adverse events, which, after careful medical consideration at the time they are evaluated, the connection with the test study medication administration appears to, with a high degree of certainty, be related to the test study medication. An adverse event may be considered probable if: (i) it follows a reasonable temporal sequence from administration; (ii) it could not be reasonably explained by the known characteristics of the patient's clinical state, environmental or toxic factors, or other modes of therapy administered to the patient; (iii) it disappears or decreases on cessation or reduction in dose. There are important exceptions when an adverse event does not disappear upon discontinuation of the study medication, yet study medication-relatedness exists; e.g. bone marrow depression, fixed study medication eruptions, and tardive dyskinesias; (iv) it follows a known response pattern to the suspected study medication; (v) it reappears upon re-challenge.

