### 6.3.2 Reporting of adverse events

As this is a clinical trial based on participant responses only, the adverse event reporting will be slightly different from other clinical trials.

The participant will report Adverse Events on a daily basis using the web-based sleep diaries. The participant will be specifically asked whether a physician is seen to evaluate the event. The primary physician may be contacted and asked to fill out a standard adverse event form. The form must be faxed within 24 hours to the study investigators, who will evaluate whether the event should be reported to the Ethics Committee and the Regulatory Authorities within 7 or 15 days, as applicable. All Serious Adverse Events will be followed up until resolution (i.e. asymptomatic, stabilisation or death).

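### The causality criteria leave an event with plausible timing, no rival cause and no observed recovery off drug without a related grade, while the same event with a rival cause is graded Possible

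*Protocol*

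**What the plan says.** Protocol section 6.3.1, under the relationship to study medication, defines five grades: Unrelated, Unlikely, Possible, Probable and Not assessable.

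- **Possible** is headed "Possible (must have first two criteria"). The first criterion is a reasonable time sequence. The second is that "it could readily have been produced by the patient's clinical state, environmental or toxic factors, or other modes of therapy administered to the patient".
- **Probable** is headed "Probable (must have first three criteria"). The criteria are a reasonable time sequence; that "it could not be reasonably explained by the known characteristics of the patient's clinical state" or by other external factors or treatments; and that "it disappears or decreases on cessation or reduction in dose". A sentence attached to the third allows exceptions for events that persist after the drug is stopped.
- **Unlikely** lists its criteria only as examples. Example (ii) has the same words as criterion (ii) of Possible. Example (iii) is the lack of a known response pattern.
- **Not assessable** takes whatever cannot be placed in the other grades.

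Section 6.3.2 sends the physician's adverse event form to the investigators, "who will evaluate whether the event should be reported to the Ethics Committee and the Regulatory Authorities within 7 or 15 days". It commits to following serious events until they resolve and says nothing similar for non-serious events.

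**The concern.** A causality scale should not give an event a weaker grade because a competing explanation has been removed. Here a competing explanation is an entry condition for Possible. An event without one can be graded as related only through Probable, and that route needs recovery off drug to have been seen.

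At stake is the meaning of the individual causality records. An event with good timing and nothing else to explain it can be filed as Not assessable, or even Unlikely, beside a Possible grade for an event with an obvious alternative cause. Anyone reading the case records, including the investigators when they evaluate an event, would be looking at a scale that points the wrong way for this profile. Section 5.3 gives, as one reason for testing a larger dose, that there is no sign of added side-effect risk at that dose, so the trial's own safety record ought to be clear.

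**Working it through.** No figure in the protocol bears on this point, so the check is to apply the criteria to each kind of event.

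**Step 1. Apply the mandatory criteria.** Timing is plausible throughout. A rival cause is treated as either present or absent.

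| Ready rival cause | Recovery off drug | Possible | Probable | Where the event lands |
|---|---|---|---|---|
| Yes | Any | Met | Fails (ii) | Possible; also fits example (ii) of Unlikely |
| No | Seen on stopping | Fails (ii) | Met | Probable |
| No | Not observed | Fails (ii) | Fails (iii) | No related grade |
| No | Did not recover after stopping, exception applies | Fails (ii) | Available through the exception | Probable |
| No | Did not recover after stopping, exception does not apply | Fails (ii) | Fails (iii) | No related grade |

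**Step 2. Place the events that have no related grade.** Unrelated does not fit, because it needs a clear outside cause. If the event follows a known response pattern, examples (i) to (iii) of Unlikely do not fit either, and it goes to Not assessable. If it follows no known pattern, example (iii) permits Unlikely. Example (iv) of Unlikely is left aside because it needs information from giving the drug again.

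**Step 3. Change one feature only.** Take plausible timing, a known response pattern and recovery not observed. With a rival cause the event is Possible. Without one it is Not assessable. Removing the alternative explanation removes the related grade.

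**Step 4. Ask whether recovery can go unobserved in this trial.**

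- Both definitions tie the judgement to the time of evaluation.
- Treatment is scheduled from Day 15 to Day 28 (sections 4.3.3 and 4.3.4), which is 28 − 15 + 1 = 14 days. Visit 4 falls on the last of these, and the diary runs for two plus two weeks (section 4.2.6). A participant who completes treatment on schedule therefore has 28 − 28 = 0 diary days planned after the end of treatment.
- Only serious events have stated follow-up to resolution (section 6.3.2).

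The third row of the table can therefore arise from a non-serious event in someone who keeps taking tablets, from an event still present at Day 28, or from a serious event evaluated before its follow-up is complete.

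**Step 5. Check for overlap.** The first row meets the mandatory criteria for Possible and also example (ii) of Unlikely, which has identical wording. Example (iv) of Unlikely and criterion (iv) of Possible are identical too. Two assessors could apply the text correctly and disagree.

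**The case against.** The strongest reply is that little depends on these grades. Section 7.5 tabulates all adverse events by type and frequency, promises narratives for serious events, and compares the proportions of participants with at least one adverse event. None of this uses relatedness, so no planned safety result changes. That stands, and it limits the point to case-level records.

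It can also be said that the gap is narrower than it looks. Section 3.4 lets a participant stop the product because of an adverse event and remain in follow-up, and serious events are followed to resolution, so recovery can be seen in such cases. The exception under Probable and the illustrative wording of Unlikely catch some others. This also stands. The exception, however, addresses events that persist after stopping. It does not reach an event graded while tablets continue. Being caught by Unlikely is no remedy for an event with good timing and no rival cause.

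A reader might infer four stronger claims, and the document supports none of them:

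- **That the lack of any planned dose reduction is the barrier.** Criterion (iii) of Probable accepts stopping alone.
- **That these are the most suspicious events.** Those that recover on stopping are more suspicious, and they can be graded Probable.
- **That every fatal event without a rival cause falls in the gap.** Whether the exception reaches such an event is arguable, since its examples are not exhaustive.
- **That 7- or 15-day reporting is decided from the grade.** Section 6.3.2 leaves it to the investigators' evaluation and names no grade as a threshold.

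**Conclusion.** The defect is on the face of section 6.3.1. The mandatory criteria give no related grade to an event with plausible timing, no ready rival cause and recovery off drug not observed. The same holds for an event that persists after stopping and falls outside the exception. An otherwise identical event with a rival cause is Possible. The wording shared by Possible and Unlikely is a second fault in the same text.

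The consequence is modest. The planned comparisons of adverse events are unaffected. The effect is on individual causality records and possibly on the investigators' reporting evaluation. The protocol gives no basis for estimating how many events would be involved.

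The conclusion assumes that the criteria the headings call mandatory are meant as written. The document does not settle whether a rival cause was intended as a condition for Possible or only as a feature that does not exclude it. Either way the text should be corrected, because it is what assessors will apply.

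**What to change.** Reconcile the definitions of Unlikely, Possible, Probable and Not assessable in section 6.3.1 so that:

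1. A rival cause is no longer a mandatory condition for Possible, though it does not rule Possible out.
2. An event with reasonable timing that misses Probable only because the effect of stopping is unknown or unobserved is graded at least Possible.
3. Unlikely and Possible no longer share a criterion, so that one event cannot satisfy both.
4. Not assessable is kept for events on which information is missing, for example on timing or on the event itself. Missing information on recovery alone should not be enough.

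The cost is a few sentences. No dose, visit or analysis changes. The downside is that a few more events will be graded as possibly related.

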#### **Probable (must have first three criteria):**

This category is applicable to those adverse events, which, after careful medical consideration at the time they are evaluated, the connection with the test study medication administration appears to, with a high degree of certainty, be related to the test study medication. An adverse event may be considered probable if: (i) it follows a reasonable temporal sequence from administration; (ii) it could not be reasonably explained by the known characteristics of the patient's clinical state, environmental or toxic factors, or other modes of therapy administered to the patient; (iii) it disappears or decreases on cessation or reduction in dose. There are important exceptions when an adverse event does not disappear upon discontinuation of the study medication, yet study medication-relatedness exists; e.g. bone marrow depression, fixed study medication eruptions, and tardive dyskinesias; (iv) it follows a known response pattern to the suspected study medication; (v) it reappears upon re-challenge.

#### **Not assessable:**

When it is not possible to assign the event to any of the criteria above categories.

### 6.3.2 Reporting of adverse events

As this is a clinical trial based on participant responses only, the adverse event reporting will be slightly different from other clinical trials.

The participant will report Adverse Events on a daily basis using the web-based sleep diaries. The participant will be specifically asked whether a physician is seen to evaluate the event. The primary physician may be contacted and asked to fill out a standard adverse event form. The form must be faxed within 24 hours to the study investigators, who will evaluate whether the event should be reported to the Ethics Committee and the Regulatory Authorities within 7 or 15 days, as applicable. All Serious Adverse Events will be followed up until resolution (i.e. asymptomatic, stabilisation or death).

## 7 STATISTICAL METHODS AND DATA MANAGEMENT

### 7.1 Study design

Randomised, double-blind, parallel group, placebo controlled trial.

